#### Intervention group

##### TASC intervention program (components)

TASC program components of integrated care and multidisciplinary team approach are discussed as below and outlined in Table 3.

**Table 3 Tab3:**
[figure not shown]
TASC components

##### Multidisciplinary team inclusive of a pharmacist

The newly assembled team consists of nursing, pharmacy, and physician care. This is a project that has brought together faculty from diverse disciplines who have not previously been involved as collaborators in post-stroke care.

A team providers meeting will be held bimonthly as a “share and learn” touch point. Patients undergoing follow up visits and remote BP monitoring will be discussed, issues identified, and an action plan generated to improve processes in care provided. Fidelity of implementation for each patient will also be reviewed with all providers. Any problems identified in providing the intervention, as well as mediators in enforcing follow ups and monitoring, will be used to inform further aims of the intervention.

Staff training will be provided to implement visually tailored infographics to patients regarding BP readings. Most recent recorded BP will be used to discuss BP goals and provide education regarding need for BP control. Remote BP monitoring team nurses will receive feedback regarding changes made to medication regimens at telehealth visits to provide guided support to patients at touch point calls. Staff schedulers and coordinators will work closely with providers and patients to schedule follow up appointments and coordinate patient care with updated contact information within discussed time frames. They will receive additional training in trial requirements and provide support for team members.

##### Remote BP monitoring

Our integrated care includes remote BP monitoring and electronic tablet devices provided through New York Presbyterian at no charge to patients with remote support including centralized telehealth nursing calls to patients for elevated readings and driven by patient feedback for frequency.

Patients randomized to telehealth services will be set up with a Philips Remote Blood Pressure Monitoring (RBPM) kit including an electronic device (Samsung tablet with 2-way video capable of telemedicine) and BP/pulse monitor and set up for remote monitoring. These services are designed to reduce disparities in technology literacy with home or remote installation as needed along with step-by-step instructions and explanations provided to each participant in their language of preference. Further, there is no need for patients to have their own technology or internet services as a tablet is included with data transfer capability. BP devices provided have been validated and calibrated for home use.

Certified nurses will touch base through phone calls with patients at intervals set to patient preference and escalate severely elevated BP readings to providers (Fig. 2). BP monitoring results as well as patient reported surveys completed on the electronic tablet are wirelessly transmitted to electronic health records and to a web-based platform (eCare Coordinator) available for the telehealth nurses and the patient’s treating clinical team to see. Critical BP or pulse readings will be shared via system alerts, at which point the call center nurse will contact the patient and assess. If unable, this is to be followed with escalation calls for elevated readings that require immediate attention to the TASC team for resolution (Fig. 2). If patients fail to measure BP data at home for a week that the device automatically transmits, they will be contacted by the call center nurse to enquire. If device trouble shooting is needed, technical assistance will be provided in person or remotely as indicated.

##### Telehealth visits by each discipline

Patients/caregivers will receive instructions regarding equipment use for telehealth video visits and the first telehealth visits after discharge will be scheduled with the nurse practitioner at 1–2 weeks (± 5 days), pharmacist at 4 and 8 weeks (± 5 days), and physician at 6 and 12 weeks (± 5 days). These visits are set at different intervals to serve as different points of visual contact with the patient and reduce duration burden of each visit. At the first visit, patients will be shown on their tablet screen an infographic tailored with their most recent BP value at hospital discharge integrated into a transitions of care management visit with a primary care nurse practitioner (see Fig. 3). The infographic will serve as the centerpiece of a motivational interview about addressing barriers to medication adherence. The pharmacist will meet with patient to review medication adherence, effectiveness through BP log, and lifestyle modifications. When not well controlled and evidence-based guideline driven, the pharmacist will adjust medications under the collaborative drug therapy management agreement. Tele-pharmacy visits are possible through the collaborative drug therapy management law in New York State which allows eligible pharmacists to formulate agreements with physicians for chronic disease management [63]. They will also address side effects and interactions of medications at these visits. Treatment of hypertension and selection of BP lowering medications will be in accordance with latest published guidelines for BP management [64]. The physician will provide patient-tailored adjustments to the care plan and monitor for any adverse events, and stroke related complications.

##### Infographics

BP infographics (Fig. 3) are to be used to provide self-management awareness and BP visual education. These will be tailored to the patient’s blood pressure at the time of discharge and shared on the screen during the first telehealth visit to drive a motivational interview guided by patient responses regarding health behaviors [59].

**Fig. 3 Fig3:**
[figure not shown]
Tailored BP infographics used to conduct motivational interview regarding control

##### Comparison group (usual care)

Participants randomized to comparison group will receive a one- and three-month post-stroke follow-up appointment. They will receive a transitional care management visit at 1-2 weeks post discharge in addition to stroke physician visits as part of the study to ensure timely follow ups. Although these may not be routinely possible, these are considered best practices. Patient-reported outcomes will be collected after consent and at three months follow-up including surveys and BP measurement.

### Study measures

Feasibility for the project will be monitored with metrics of at least one subject per week to be recruited, weekly and monthly recruitment rates assessed with estimates of these rates gathered at the end of the study. We will assess feasibility of randomization with expected targets of at least 70% of all eligible patients recruited during the enrollment period. We will also assess adherence and retention rates, with expected adherence of at least 70% to at least one video visit in each arm, and retention rates of at least 70% at study completion as stop-go criteria.

Since this is a pilot feasibility study, a sample size calculation was not performed. It is felt that *n* = 50 will be a large enough sample to inform about the practicalities of intervention delivery among patients returning home after an acute stroke. Specifically, with *n* = 25, there is about 85% power at 5% significance (one-sided) to demonstrate an adherence rate of 75% in an arm against a null rate of 50%. We note that in COMPASS-TC study [46] only 35% attended a clinic visit. Therefore, setting the null rate at 50% is reasonable.

Fidelity of implementation will be assessed using a brief checklist at each patient visit by each discipline. An internally designed and validated survey, Telemedicine Satisfaction and Usefulness Questionnaire (TSUQ) [65] provides measures of patient satisfaction and will be collected at 3 months among intervention patients to assess patient satisfaction with telehealth (Table 4). Self-Assessment of Interdisciplinary Research Competencies will be surveyed at the beginning and end of the project to establish progress and satisfaction among TASC providers and investigators in this collaboration [66–68].

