**Fig. 2 Fig2:**
[figure not shown]
Remote BP patient monitoring overview of system workflow

We will randomize 25 patients to the TASC intervention, including remote blood pressure monitoring, and 25 patients to usual care. Feasibility measures of interdisciplinary team competency, recruitment, retention, fidelity of implementation, and telehealth patient satisfaction surveys will be assessed in the intervention arm.

To our knowledge, no studies providing accessible integrated care including telehealth and remote BP monitoring with multidisciplinary teams including pharmacy and nursing have been conducted. Such an intervention may reduce racial disparities in post-stroke BP control by providing access to care and facilitating self-efficacy to improve health outcomes.

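### The stated 85% power rests on a cut-off of 17/25, which slightly exceeds the 5% level and falls short of the protocol's own 70% go criterion; a cut-off that meets both has 73% power

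*Protocol article*

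**What the plan says.** Under Study measures, the protocol article says that no sample size calculation was made because this is a pilot, and that 50 patients are thought enough to learn about delivery. It then adds one quantitative support: with 25 patients, "there is about 85% power at 5% significance (one-sided) to demonstrate an adherence rate of 75% in an arm". The null is 50%, chosen because clinic attendance in an earlier pragmatic trial was only 35%: "Therefore, setting the null rate at 50% is reasonable". Study design and overview confirms the arm size: "We will randomize 25 patients to the TASC intervention, including remote blood pressure monitoring, and 25 patients to usual care".

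The same section sets the stop-go criteria. One of them is "expected adherence of at least 70% to at least one video visit in each arm"; another is retention of at least 70%. The article names no test or cut-off for the power figure and gives no probability of meeting the adherence criterion.

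**The concern.** Two statements about the same outcome stand close together and do not fit. The power sentence implies some number of adherent patients out of 25 at which adherence counts as demonstrated. The stop-go criterion implies another. With only 25 patients, moving the cut-off by one patient changes both error and power by several points, so it matters which number lies behind the 85%.

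Adherence to at least one video visit is part of the primary feasibility outcome (Abstract, Methods), and Statistical analysis says that the decision to pursue a further trial rests on feasibility. If the 85% belongs to a cut-off that the go criterion would reject, it is too optimistic a guide to how the progression decision will behave. A stop could then be read as infeasibility when true adherence was at the 75% alternative.

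**Working it through.** **Inputs** (Study measures, unless noted): n = 25 per arm (also Study design and overview); null rate p0 = 0.50; alternative p1 = 0.75 in one arm; one-sided level 0.05; go criterion of at least 70% in each arm.

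**1. Reproducing the stated figure.** The uncorrected one-sided z-test rejects when z = (x − n·p0)/√(n·p0·(1 − p0)) exceeds 1.645. Here n·p0 = 12.5 and the standard deviation is 2.5.
- x = 16: z = (16 − 12.5)/2.5 = 1.40, no rejection.
- x = 17: z = (17 − 12.5)/2.5 = 1.80, rejection.

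So the cut-off is 17/25. The usual normal-approximation power is Φ([(p1 − p0)√n − 1.645·√(p0(1 − p0))]/√(p1(1 − p1))) = Φ((1.25 − 0.8225)/0.433) = 83.8%, and the exact binomial power of that cut-off is 85.06%. Either is consistent with about 85%.

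**2. Exact properties of the candidate cut-offs.** With P(X ≥ r) = Σ C(25,k) p^k (1 − p)^(25−k), summed over k = r to 25:

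| Cut-off | Observed rate | Error at a true 50% | Power at a true 75% |
|---|---|---|---|
| 16/25 | 64% | 11.48% | 92.87% |
| 17/25 | 68% | 5.39% | 85.06% |
| 18/25 | 72% | 2.16% | 72.65% |
| 19/25 | 76% | 0.73% | 56.11% |

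No fixed cut-off gives both 85% power and a true level of at most 5%. The smallest cut-off that holds 5% is 18/25.

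**3. The go criterion.** 0.70 × 25 = 17.5, so at least 18 of 25 are needed. A result of exactly 17/25 passes the test behind the 85% but fails the criterion. At a true 75%, its probability is 85.06% − 72.65% = 12.41%, which is the whole gap between the two figures.

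**4. Each arm.** The power sentence covers one arm; the criterion must be met in both. If both arms have the same true rate, are independent and have all 25 patients in the denominator:

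| True adherence | One arm passes | Both arms pass |
|---|---|---|
| 70% | 51.2% | 26.2% |
| 75% | 72.65% | 0.7265² = 52.8% |
| 80% | 89.1% | 79.4% |
| 85% | 97.5% | 95.0% |

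A pass probability of 85% needs a true rate of 78.5% in a single arm, or 81.4% for both arms together.

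**5. If the denominator shrinks.** With 24 patients, 70% means 17 (0.70 × 24 = 16.8), and the exact 5% test also needs 17. With 23, 70% still means 17 (16.1), but the exact test needs only 16 (level 4.66%). The test and the criterion therefore coincide at 25 and 24 but not at 23.

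**The case against.** The figure has a recognisable source. It follows from the protocol's own inputs under a standard large-sample test, the text says only that it is approximate, and an excess of 0.4 points over a nominal 5% is small in a pilot. A reader might infer that the 85% is simply a miscalculation. The document does not support that, because it never commits to an exact test.

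A reader might also infer that the protocol promises an 85% chance of meeting the go criterion. It does not: the power sentence concerns a test of 50%, the 70% threshold is a separate criterion on the observed rate, and nothing links the two.

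Nor can one say that the trial is planned at 75% adherence in both arms and so faces a coin-flip. The 75% is an alternative for one arm; the stated expectation is 70% or more in each. The joint figure rests on assumptions and moves quickly with the true rate, as the table in the working shows. Multiplying further by a chance of adequate retention would be weaker still. The article gives no alternative rate for retention, and patients who are retained have probably attended a visit, so independence is doubtful.

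Finally, the sample size was not derived from this calculation, so a corrected figure would change neither n nor conduct. All of this stands, and it limits the weight of the point. It does not remove the mismatch: the level and the power as stated cannot both hold exactly with 25 patients, and the cut-off that yields the 85% fails a criterion set in the same section. Both statements are in the article, so this is not a detail left to a fuller document.

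**Conclusion.** The concern holds in a limited form. The stated power is obtained with a cut-off of 17/25, whose true one-sided error is 5.4%. Holding 5% requires 18/25, with an attained level of 2.2% and power of 73%, about 12 points below the stated figure. Because 17/25 is 68%, the 85% does not describe the adherence rule that decides progression. That rule passes 73% of the time per arm at a true 75%, whichever test is preferred, provided all 25 patients are in the denominator. The figure of about 53% for both arms further assumes independent arms that each have a true rate of 75%. This is a correction to make, but not a critical one: it changes how the design's performance is described, not the sample size or the criterion.

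**What to change.** In Study measures, replace the power sentence with wording such as:

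> With 25 patients per arm, an exact one-sided 5% binomial test rejects an adherence rate of 50% when 18 or more adhere (attained level 2.2%); power is 73% at a true rate of 75%. This coincides with the 70% go criterion when all 25 are evaluable. If both arms truly have 75% adherence and are independent, both meet the criterion with probability about 53%.

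Keep the go rule as at least 70% of evaluable patients in each arm, and do not fix it at 18/25. The Withdrawal section removes patients who are unexpectedly discharged to a nursing facility, so the denominator may fall below 25, and a fixed count would then no longer equal 70%.

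The cost is a less favourable stated power. No extra patients are needed, and the criterion itself does not change.

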**Table 4 Tab4:**
[figure not shown]
List of study measures

Patients will receive BP monitors at different times to meet ethical and clinical standards, either at the start for patients in the intervention arm or at study end in the usual care arm. RBPM will be conducted among participants in the intervention arm from time of discharge through to 3 months. Readings from the first 24 h at 3 months in control will be collected.

Patient-reported outcomes will be collected using the PROMIS tools (self-efficacy of medication adherence and treatment, Neuro-QOL Depression, and Cognitive Function) as well as patient activation measure (PAM) at time of consent and at 3 months among all participants. The effect of empowering stroke survivors’ self-management can be assessed through surveys of medication adherence and treatment self-efficacy, and activation in health behaviors.

### Data collection

Patient demographics, social determinants of health (age, education, race/ethnicity, address, income, insurance type, along with food, housing, and income security), internet and electronic devices access questions, and medical characteristics (risk factors, comorbidity burden, stroke adjudication) will be collected from the patient and electronic medical records in a data collection form at discharge and at 3 months.

RBPM will be set up for the intervention arm through to 3 months. Patients in the usual care arm will receive the BP monitoring kit with remote assistance at 11 weeks and provide readings at 3 months for outcome assessment. They will also be aided through the remote monitoring team with survey completion if needed. All completed surveys and BP readings will be converted to transferrable format and transmitted via the online platform to REDCap database at 3 months for study completion. Electronic medical records will also be revisited at study end for any additional surveys conducted during patient visits for clinical screening and management purposes.

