### Randomization and blinding

We will randomize patients (1:1) to intervention versus usual care using a computer-generated block design for parallel assignment. The randomization allocation sequence will be developed by a statistician not involved in the enrollment procedures. The outcomes assessors will be blinded after participant assignment to intervention We plan to stratify based on race to assure that the groups are balanced with respect to baseline risk and sample.

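### The unqualified statement that outcome assessors are blinded does not hold for 3-month surveys that usual-care patients complete with help from the remote monitoring team

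*Protocol article*

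**What the plan says.** Under Randomization and blinding, the article makes one general statement: "The outcomes assessors will be blinded after participant assignment to intervention". It does not say which outcomes or which staff this covers.

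Under Data collection, it describes how the usual-care arm reaches the 3-month assessment: "Patients in the usual care arm will receive the BP monitoring kit with remote assistance at 11 weeks and provide readings at 3 months for" (the sentence ends by giving assessment of the outcome as the purpose). The next sentence reads: "They will also be aided through the remote monitoring team with survey completion if needed".

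The same team's role in the intervention is set out elsewhere:

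- Remote BP monitoring: "Certified nurses will touch base through phone calls with patients at intervals set to patient preference and escalate severely elevated BP readings to providers".
- Multidisciplinary team inclusive of a pharmacist: "Remote BP monitoring team nurses will receive feedback regarding changes made to medication regimens at telehealth visits".
- Study measures: "RBPM will be conducted among participants in the intervention arm from time of discharge through to 3 months".

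The surveys concerned are the PROMIS self-efficacy measures, Neuro-QOL Depression, Cognitive Function, and the last in the list, "as well as patient activation measure (PAM) at time of consent and at 3 months among all participants". The Abstract names medication-adherence self-efficacy at 3 months as a secondary outcome.

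**The concern.** The article promises blinded outcome assessment and also gives staff who deliver the intervention a part in collecting the 3-month patient-reported outcomes. A helper who reads out, explains or enters items can influence the answers, and self-efficacy scores are open to social desirability and interviewer effects. The hypothesis stated under Secondary aims includes better self-efficacy with TASC than with usual care, so influence in one arm only would bear directly on that comparison.

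Two things are at stake. First, a report that repeats the blinding statement would describe these outcomes inaccurately. Second, the pilot is meant to inform the protocol of a definitive trial, so an unblinded collection step labelled as blinded could carry over. Data management, monitoring, and safety reporting says that survey data will not be verified, so no later check would reveal a helper's influence.

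**Working it through.** No figure in the article bears on this point. The check sets the relevant statements side by side.

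**1. Who is helped?** The subject of the sentence before the help statement is the patients in the usual-care arm, so the help is described for them. Nothing in the article says that the monitoring team helps TASC patients with surveys.

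**2. Does the helper know the arm?** Yes, by two routes.

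| Source of knowledge | TASC | Usual care |
|---|---|---|
| Time the kit is set up | from discharge | 11 weeks |
| Nurse calls and feedback on medication changes during follow-up | yes | none described before the kit arrives |

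The set-up time alone reveals the allocation.

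**3. Can both statements hold?** For surveys completed without help, the monitoring team plays no part. For assisted surveys, someone who knows the arm takes part in producing the outcome, and the article does not confine that part to technical matters. The unqualified blinding statement is therefore not met for these surveys.

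**4. How many patients?** Study design and overview gives 25 patients per arm.

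- Upper bound: 25 of 50 randomized, i.e. 25/50 = 50% of the trial and 25/25 = 100% of the usual-care arm, if every usual-care patient needed help.
- Lower bound: 0, if none did.

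The article gives no rate of need, so the range cannot be narrowed.

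**5. Which outcomes?**

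- Affected if assisted: self-efficacy, depression, cognitive function and patient activation at 3 months.
- Not affected: recruitment, video-visit adherence and retention, which make up the primary outcome.
- Not affected: the other secondary outcome, telehealth satisfaction. Study measures collects it in intervention patients only, and the help is described for usual care.

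**6. Which direction?** It cannot be determined. A usual-care patient wishing to please a supportive nurse might score higher, which would narrow the difference between arms. A helper who probes for difficulties, or expects usual care to do worse, might lower the score and widen it. The article gives no basis for choosing.

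**7. Would the outcomes be blinded without this help?** No. The respondent produces the score and knows the arm, since one group has had the kit, nurse calls and pharmacist visits for 3 months. The help adds a second, arm-dependent departure from blinding to one that already exists.

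**The case against.** The strongest reply is that aiding completion is not assessing. Data integration has patients complete surveys on the tablet and send them automatically. The help sentence follows directly on the delivery of an unfamiliar kit with remote assistance, so help in working the tablet is a natural reading. The outcomes assessors of the blinding statement may be other people. Their identity, and the mode of survey administration, are details that an article may leave to the full protocol. The trial is also a feasibility pilot: Statistical analysis bases the decision on a further trial on feasibility and calls all other measures hypothesis generating.

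Much of this stands. It limits the weight of the point, and the help may be partly or wholly technical. It does not remove the point, because the text refers to completing the surveys, sets no technical limit, and names a team that cannot be blind. The issue is not an omitted detail: the article makes an unqualified claim and then describes a procedure that does not fit it.

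A reader might infer more than the article supports:

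- **TASC patients answer with help from the nurses who have coached them, so the bias favours TASC.** The help sentence concerns usual-care patients only. Contact with nurses during follow-up is part of the intervention, not of outcome assessment.
- **All 50 patients are exposed.** The ceiling is the 25 in usual care.
- **Help will commonly be needed because patients with aphasia or caregivers can enrol.** Patients who lack capacity includes those with caregivers only if they can answer questions about their own health, and Approach and consent deals with representatives giving consent, not completing surveys. Need is plausible, but its frequency is unknown.
- **The monitoring team's help is what unblinds these outcomes.** They would be unblinded without it.

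**Conclusion.** The point holds in a limited form. As written, the assessor-blinding statement is not true of 3-month patient-reported outcomes that usual-care patients complete with the monitoring team's help, and the description of help for one arm only leaves room for a difference in assistance between arms. Between 0 and 25 patients are affected, with bias of unknown size and direction. One secondary outcome, medication-adherence self-efficacy, and several additional survey measures are involved. The stop-go criteria and the primary feasibility outcomes are not.

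This rests on two readings: that the help sentence refers to the usual-care patients of the sentence before it, and that the help is not confined to operating the device. If the full protocol confines it to the device, the concern about helper influence largely falls away. The need to narrow the blinding statement would remain, because respondents know their arm.

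**What to change.** 1. Under Data collection, limit the remote monitoring team to technical support with the kit.
2. Have any help with survey content given in both arms, under one neutral script, by existing research staff who are outside that team and do not schedule arm-specific visits. The bilingual coordinators described under Recruitment cannot simply be assumed to be blind: the section on the multidisciplinary team has schedulers and coordinators arranging follow-up appointments, and anyone who books pharmacist visits would know the arm.
3. Record for each 3-month survey whether help was given and by whom, so that assistance can be compared between arms.
4. Whether or not items 1 to 3 are adopted, narrow the statement under Randomization and blinding to the steps that are actually blinded. Extraction and analysis of the BP data are possible examples, if the sponsor confirms them. Describe the patient-reported outcomes as unblinded.

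The cost is the reassignment of a small task, a short script, one extra data item, and one revised sentence. The downside is slightly less convenience than using nurses already in contact with the patient, and a less favourable blinding statement.
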